## Abstract

**Background:**

Dual antiplatelet therapy (DAPT) with aspirin and a P2Y12 inhibitor is the standard of care after coronary stenting, including coronary stenting involving bioresorbable scaffolds (BRSs). Current clinical guidelines recommend at least 12 months of DAPT after BRS implantation. However, the correlation between prolonged DAPT and net clinical benefits remains unknown.

**Methods:**

The SPARTA trial is designed to be a prospective, randomized, parallel-group, clinical trial. It aims to compare the benefits and risks of DAPT applied for either 12 or 36 months after XINSORB BRS implantation. The primary endpoints are the incidence of the composite endpoint of major adverse cardiac events (MACEs), including all-cause death, any myocardial infarction (MI), and all revascularizations, as well as Bleeding Academic Research Consortium Definition (BARC) type 3 or 5 bleeding events. The secondary endpoints of the study include the device-oriented composite endpoint of target lesion failure (defined as cardiac death, target vessel-related MI, or ischemia-driven target lesion revascularization), target vessel failure (defined as cardiac death, MI, or ischemia-driven target vessel revascularization), scaffold thrombosis, and minor bleeding events. This trial will enroll 2106 subjects treated with the XINSORB BRS only. All subjects will receive DAPT after the index procedure for 12 (± 1) months. Subjects without MACEs or major bleeding will be randomized to receive either 24 additional months of DAPT or aspirin alone.

**Discussion:**

This trial is designed to investigate the impact of extending the duration of DAPT up to 3 years after XINSORB BRS implantation by investigating the balance of risks and benefits in a broad population of treated patients.

**Trial registration:**

ClinicalTrials.gov NCT04501900. Registered on 6 August 2020.

**Supplementary Information:**

The online version contains supplementary material available at 10.1186/s13063-022-07028-8.

## Administrative information

Note: the numbers in curly brackets in this protocol refer to SPIRIT checklist item numbers. The order of the items has been modified to group similar items (see http://www.equator-network.org/reporting-guidelines/spirit-2013-statement-defining-standard-protocol-items-for-clinical-trials/).

## Introduction

### Background and rationale {6a}

Bioresorbable scaffolds (BRSs, referring mainly to the Abbott biovascular scaffold [BVS], Abbott Vascular, Santa Clara, CA, US) are associated with increased risks of target lesion failure (TLF) and scaffold thrombosis according to recently published papers [1–3]. However, additional events of TLF and scaffold thrombosis related to BVSs were comparable to those observed with metallic Xience stents (Abbott Vascular, Santa Clara, CA, US) beyond the 3-year follow-up [4]. It was hypothesized that inflammation triggered by metabolites of poly-L-lactic acid (PLLA) would not terminate until full absorption of the struts. As a result, prolonged dual antiplatelet therapy (DAPT) was recommended after BRS implantation [5]. The XINSORB bioresorbable sirolimus-eluting scaffold (HuaAn Biotech, Shandong, China) is a contemporary BRS. It was approved by the China Food and Drug Administration (CFDA) in March 2020 because of its favorable long-term clinical outcomes [6–10]. More than 50% of XINSORB BRS-treated patients were still on DAPT at the 3-year follow-up. It was believed that prolonged DAPT played a critical role in maintaining low rates of TLF and scaffold thrombosis associated with the XINSORB BRS.

The results from the DAPT study showed that when compared with aspirin therapy alone, DAPT beyond 1 year after placement of a drug-eluting stent (DES) significantly reduced the risks of stent thrombosis and major adverse cardiovascular and cerebrovascular events [11]. However, prolonged DAPT did not show additional benefits in ischemia events compared with standard DAPT in stable coronary disease after DES deployment [11–14]. Furthermore, extending therapy beyond 1 year conferred an increased risk of bleeding. Any incremental benefit with regard to a reduction in the risk of clinical ischemia events and late stent thrombosis must therefore be weighed against an increased risk of bleeding. The use of DAPT in the DES era would not affect BRSs easily or identically. Hence, the correlation between ischemia and bleeding after BRS implantation remains unknown.

Given the lack of adequate randomized trial data, there is considerable uncertainty in the duration of DAPT after BRS implantation. The aim of the SPARTA trial is to investigate the impact of extending DAPT beyond 1 year after XINSORB BRS implantation by investigating the balance of risks and benefits in a broad population of treated patients.

### Trial design {8}

The SPARTA trial is designed to be a prospective, randomized, parallel-group, clinical trial. We will test the hypothesis that 36 months is superior to 12 months of DAPT.

### Objectives {7}

The primary objective of the SPARTA trial (NCT04501900) is to compare the effectiveness of 36 (prolonged) versus 12 (standard) months of DAPT after XINSORB BRS implantation. The safety objective is to compare the risk of Bleeding Academic Research Consortium Definition (BARC) type 3 or 5 bleeding in patients treated with 36 versus 12 months of DAPT [15].

## Methods

### Study settings {9}

The study is a multicenter clinical study carried out at approximately 30 sites in China. All sites will be academic hospitals (Refer to supplementary materials).

### Eligibility criteria {10}

Study subjects diagnosed with stable, unstable ischemic coronary disease or myocardial infarction (MI) planning to undergo percutaneous coronary intervention (PCI), and no contradiction to prolonged DAPT are eligible for this trial. All subjects will provide written informed consent to participate. Subjects will be enrolled in the study after 12 months (± 1 month) of the DAPT post index procedure. Subjects will be randomized to either discontinue a P2Y12 inhibitor (clopidogrel or ticagrelor) (12 months total) or receive a P2Y12 inhibitor for an additional 24 months (36 months total). Aspirin will be maintained throughout the entire study and can be replaced by cilostazol or indobufen if subjects are intolerant. The dosage of antiplatelet drugs will be determined according to the local standard of practice. Subjects will be treated with the XINSORB BRS only. Figure 1 shows the consort flow diagram of the study.

**Fig. 1 Fig1:**
[figure not shown]
Consort flow diagram

The major exclusion criteria included (1) cardiogenetic shock; (2) chronic heart failure with a left ventricular ejection fraction less than 30%; (3) subjects on warfarin or similar oral anticoagulation therapy; (4) known allergy or intolerance to aspirin, any P2Y12 inhibitor, heparin, contrast media, sirolimus, PLLA, or other allergens; (5) malignancies and other comorbid conditions with a life expectancy less than 5 years; (6) subjects treated with both BRS and DES; and (7) subjects who planned to receive staged PCI. Given the special properties and sizes of the BRSs, lesions with a reference vessel diameter of 2.75 to 3.5 mm will be included. Lesions located in the left main artery or less than 3 mm to the ostium of the left anterior descending (LAD) artery, the left circumflex (LCX) artery, or the right coronary artery (RCA) and bifurcation lesions (Medina 1,1,1) planning to be treated with two stents strategy will be excluded. The inclusion and exclusion criteria are detailed in Table 1.

**Table 1 Tab1:** Inclusion and exclusion criteria

Inclusion criteria	(1). Subjects who received the XINSORB BRS and were then treated with DAPT for 12 months
	(2). Written informed consent obtained from the subjects
	(3). Candidates qualified for coronary bypass surgery
	(4). Lesions with a reference vessel diameter of 2.75 to 3.5 mm
Exclusion criteria	(1). Age ≤ 18 years
	(2). Cardiogenetic shock
	(3). Chronic heart failure with a left ventricular ejection fraction ≤ 30%
	(4). Oral anticoagulation therapy
	(5). Known allergy or intolerance to the study medications
	(6). Malignancies and other comorbid conditions with a life expectancy less than 5 years
	(7). Subjects treated with both BRS and DES during the index procedure
	(8). Pregnant women
	(9). Planned to receive staged PCI
	(10). Contemporaneous enrollment in a different clinical trial
	(11). Any revascularization within 1 year
	(12). Planned surgery necessitating the discontinuation of antiplatelet therapy within 36 months after enrollment
	(13). Unprotected left main artery
	(14). Lesions located at the ostium of the main coronary artery
	(15). Bifurcation lesions (Medina 1,1,1) planning to be treated with the two stents strategy

A total of 2106 subjects will be enrolled and randomized at approximately 30 centers in China in this manufacturer-run postmarketing study.

### Who will obtain informed consent? {26a}

Authorized physicians will obtain informed consent from the subjects before randomization.

### Additional consent provisions for the collection and use of participant data and biological specimens {26b}

The study will collect electrocardiography data and biological specimens, such as blood and urine, for liver and renal function, routine blood, blood cholesterol, and cardiac biomarker analysis, with the written consent of study subjects.

### Explanation for the choice of comparators {6b}

The results from the DAPT study showed that when compared with aspirin therapy alone, DAPT beyond 1 year after placement of a DES significantly reduced the risks of stent thrombosis and major adverse cardiovascular and cerebrovascular events. However, extending therapy beyond 1 year conferred an increased risk of bleeding. However, the use of DAPT in the DES era would not affect BRSs easily or identically. Hence, the correlation between ischemia and bleeding after BRS implantation remains unknown. Given the lack of adequate randomized trial data, there is considerable uncertainty in the duration of DAPT after BRS implantation. The aim of the SPARTA trial is to investigate the impact of extending DAPT beyond 1 year after XINSORB BRS implantation by investigating the balance of risks and benefits in a broad population of treated patients.

#### Scaffolds

As previously reported, the XINSORB BRS is composed of PLLA as its backbone. Poly-D-L-lactic acid (PDLLA) mixed with PLLA carrying sirolimus is coated on its struts. The dose of sirolimus administered was 8–16 μg/mm, depending on the length of the BRS. The thickness of the strut is 160 μm. The sizes of the XINSORB BRSs that will be used in this study are 2.75, 3.0, and 3.5 mm in diameter and 12, 15, 18, 23, and 28 mm in length.

### Intervention description {11a}

All subjects will take a loading dose of 300 mg clopidogrel or 180 mg ticagrelor plus 300 mg aspirin within 24 h before intervention. After the index procedure, a daily dose of a P2Y12 inhibitor (75 mg clopidogrel per day or 180 mg ticagrelor twice a day) as well as 100 mg aspirin per day will be administered over 12 months after the index procedure (observational period). Aspirin can be replaced by cilostazol (50 mg twice a day) or indobufen (100 mg twice a day) if subjects have a history of a gastric ulcer or bleeding. For the subjects who are eligible for randomization at 12 months (± 1 month), the prerandomization daily dose of the P2Y12 inhibitor will be continued or discontinued based on the randomization arm. Aspirin will be maintained for the duration of treatment. Subjects who switch from one type of P2Y12 inhibitor to another are eligible for enrollment if they have not changed within 6 months before randomization. All drugs will be prescribed to subjects routinely at the outpatient department of each center. Regular records of drug usage will be made throughout the entire study by investigators. Compliance will be reviewed by phone calls to subjects every 3 months from physicians to reconfirm the daily dose of each drug. Prasugrel has not yet been approved for the treatment of coronary artery disease in China.

All XINSORB BRS-treated subjects who are receiving 12 months (± 1 month) of the DAPT post index procedure and who are event-free (from death, MI, stroke, repeat revascularization, scaffold thrombosis, and BARC type 3 or 5 bleeding events) and who are compliant with DAPT (defined as no interruption more than 14 days) are eligible for randomization. The subjects will be randomized at a 1:1 ratio to receive either aspirin alone or a continuation of DAPT for an additional 24 months.

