### Criteria for discontinuing or modifying allocated interventions {11b}

There will be no special criteria for discontinuing or modifying allocated interventions.

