### Relevant concomitant care permitted or prohibited during the trial {11d}

Subjects with ischemic symptoms will be admitted to the hospital. Repeat interventions were performed if lesions with restenosis were revealed. DAPT will be stopped if any BARC type 3 or 5 bleeding events occur and relevant care will be provided.

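### The retention section excludes subjects after any event or deviation, which conflicts with 24-month follow-up of all randomized subjects and ITT; separately, the ticagrelor maintenance dose is ambiguous by a factor of two

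*Protocol article*

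**What the plan says.** **Exclusion and analysis.** Section {18b} of the protocol article, on retention and complete follow-up, says that a subject who has any event, or who departs from the protocol, is taken out of the study. Its next sentence says that such subjects continue to be monitored and looked after to the end of the study. The Follow-up subsection follows all randomized subjects for 24 months. Section {20a} places all analyses on the ITT population, and {20c} keeps ITT even where there are crossovers.

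**Dose.** Section {11a} gives the loads: "All subjects will take a loading dose of 300 mg clopidogrel or 180 mg ticagrelor plus 300 mg aspirin". It then introduces P2Y12 maintenance as a daily dose, with the amounts in brackets: "75 mg clopidogrel per day or 180 mg ticagrelor twice a day". Aspirin maintenance follows in the same sentence: "as well as 100 mg aspirin per day will be administered over 12 months". The substitutes come next: "Aspirin can be replaced by cilostazol (50 mg twice a day) or indobufen (100 mg twice a day". At randomization, "the prerandomization daily dose of the P2Y12 inhibitor will be continued or discontinued based on the randomization arm".

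**Two neighbouring wordings.** Section {10} says: "The dosage of antiplatelet drugs will be determined according to the local standard of practice". Section {11b} says: "There will be no special criteria for discontinuing or modifying allocated interventions". Section {11d} says: "DAPT will be stopped if any BARC type 3 or 5 bleeding events occur".

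**The concern.** Events and deviations after randomization are what an ITT analysis exists to retain. A site that acts on {18b} could close a subject's endpoint record at the first bleed, MACE or deviation, and the ITT analysis would then lack the later outcomes. The loss need not be equal between arms. The Introduction reports that extending DAPT beyond 1 year after a drug-eluting stent raised the bleeding risk. If that also holds here, exclusions triggered by bleeding would fall more often in the prolonged arm. If subjects who have bled also carry a higher later MACE risk, losing that follow-up would flatter prolonged DAPT, which is the direction of the superiority hypothesis in {8}.

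The dose line matters for a different reason. Whatever dose a subject takes before randomization is continued in one arm only, for 24 months, and BARC type 3 or 5 bleeding is the stated safety objective in {7}. A maintenance line that can be read in two ways, one double the other, should not go to about 30 sites.

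**Working it through.** **1. The exclusion sentence beside the other rules.** The protocol article states no figure on this point, so the check compares texts. Three kinds of subject are taken through each rule.

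| Randomized subject | Follow-up, {20a}, {20c} | {18b} read literally |
|---|---|---|
| Has a BARC type 3 bleed, stops DAPT under {11d}, later has an MI | Followed to 24 months; the MI counts as MACE | Excluded at the bleed; the bleed is already recorded, but the later MI may not be analysed |
| Crosses over to the other treatment, later has any endpoint event | Kept in the allocated arm | Excluded at the crossover, which is itself a deviation |
| Has a revascularization as first MACE, later dies of a cardiac cause or has a major bleed | First MACE counts for the primary endpoint; the later death or bleed counts for secondary endpoints | First MACE is already recorded; the later death or bleed may not be analysed |

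The two columns differ in every row, always on the later outcome and never on the event that triggers exclusion. For the primary time-to-event analysis, the exposed data are MACE after a bleed or a deviation. For secondary endpoints they also include events after a first MACE.

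The continued-monitoring sentence in {18b} does not settle this. It says that subjects are watched and cared for. It does not say that what is observed enters the trial's analysis.

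**2. The ticagrelor line.** All inputs are from {11a}. The ratio is daily maintenance divided by the loading dose.

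- Clopidogrel: 75 / 300 = 0.25.
- Aspirin: 100 / 300 = 0.33.
- Ticagrelor, 180 mg read as the amount per dose: 2 × 180 = 360 mg/day; 360 / 180 = 2.0.
- Ticagrelor, 180 mg read as the daily total: 180 mg/day, or 180 / 2 = 90 mg per dose; 180 / 180 = 1.0.

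The words that introduce the bracket, a daily dose, allow the second reading. The form of words favours the first: the cilostazol and indobufen entries use mg twice a day, and there it means the amount per dose. On that reading ticagrelor is the only one of the three drugs whose daily maintenance exceeds its load. The two readings differ by 360 / 180 = 2.

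**3. What cannot be computed.** The article gives no share of subjects on ticagrelor, no expected bleeding rate and no deviation rate by arm. The Discussion says that earlier BRS trials collected no bleeding data. Neither a number of affected subjects nor an effect on MACE or bleeding follows from the text.

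**The case against.** **On exclusion.** The Follow-up subsection, {20a} and {20c} are specific and agree with each other, whereas {18b} is one loose sentence in a section on retention. An analyst would probably follow the specific statements. The sentence may also describe only the year before randomization, when {11a} already bars subjects with an event or a DAPT interruption of more than 14 days. Both points have force and lower the chance of harm. They do not remove the conflict: {18b} carries no such limit, its subject is complete follow-up, and site staff rather than analysts would act on it. A reader might go further and infer that the trial will delete primary endpoint events or run a per-protocol analysis. The documents do not support that. The triggering event is recorded before any exclusion, and ITT is stated twice.

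**On the dose.** Nothing in the article requires maintenance-to-load ratios to agree across drugs, or forbids maintenance above the load, so a ratio of 2.0 does not prove an error. A reader might infer that the protocol prescribes a double dose. The text does not establish this: the daily-dose wording permits 180 mg/day, and no intended figure is given. The local-practice rule in {10} and the routine outpatient prescribing in {11a} also make it less likely that a site would follow a wrong figure. What remains is an ambiguous line that needs checking.

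**On the neighbouring wordings.** A reader might call {10} against {11a}, and {11b} against {11d}, direct contradictions. Both pairs can be reconciled. The listed doses can be usual values with local practice deciding, and a site that reads both {11b} and {11d} would stop DAPT after a BARC type 3 or 5 bleed. These are editorial matters.

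**Conclusion.** The main point holds as a conflict in the text. Section {18b} states an exclusion rule that cannot stand beside 24-month follow-up of all randomized subjects and ITT despite crossovers. What is at risk is outcomes after a bleed, an event or a deviation; the triggering event itself is safe. The direction of any bias is not fixed. The scenario favouring prolonged DAPT assumes more bleeding in that arm and a raised later MACE risk after a bleed. Deviations could occur in either arm.

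The secondary point holds as an ambiguity of 180 against 360 mg/day. The wording leans towards 360, but the article does not show which was meant. Practical harm depends on a site following the written figure instead of local practice, and the documents give no evidence that one would.

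Neither point has a computable effect on the results. Both should be corrected before enrolment, mainly because the correction costs almost nothing and the exclusion rule, if followed, would undermine the stated analysis.

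**What to change.** 1. Replace the exclusion sentence in {18b} with: *Randomized subjects who have an event, deviate from the protocol or stop DAPT remain in follow-up to 24 months and in the ITT analysis.* If exclusion was meant only for the 12 months before randomization, say so there.
2. Verify the ticagrelor maintenance figure in {11a} and state it both in mg per dose and in mg per day, before sites open.
3. Editorial: in {11b}, cross-refer to the {11d} rule that DAPT stops after a BARC type 3 or 5 bleed. In {10} or {11a}, state that the listed doses are usual values and that local practice decides.

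The cost is a text amendment. Under Trial status the article says that the study has not begun. Sample size, visits, endpoints and analysis method are unchanged.

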### Criteria for discontinuing or modifying allocated interventions {11b}

There will be no special criteria for discontinuing or modifying allocated interventions.

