#### Follow-up

All randomized subjects will be followed up for 24 months after randomization. The subjects who are randomized to the prolonged DAPT arm will receive a daily dose of a P2Y12 inhibitor and aspirin for a total of 3 years (± 1 month). The other subjects will receive aspirin alone. All subjects will be contacted at 3, 6, 9, 12, 15, 18, 21, 24, 27, 30, 33, and 36 months through a phone call or office visit. Demographic, clinical, and procedural information at the time of enrollment as well as subsequent clinical endpoints, serious adverse events, concomitant medications, and antiplatelet therapy compliance will be obtained. Data will be continuously collected until the end of the study. All endpoints and events that occur after randomization will be adjudicated by an independent clinical events committee who is blinded to the study.

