### Outcomes {12}

The primary endpoint of this study is the incidence of the composite endpoint, including all-cause death, any MI, and all revascularizations (major adverse cardiac events, MACEs) 24 months after randomization. MIs will be classified and adjudicated according to the Academic Research Consortium (ARC) definitions [16].

The secondary endpoints of the study include the device-oriented composite endpoint (DoCE) of TLF (cardiac death, target vessel-related myocardial infarction [TV-MI], or ischemia-driven target lesion revascularization [ID-TLR]), target vessel failure (TVF; cardiac death, MI, or ischemia-driven target vessel revascularization [ID-TVR]), the individual component endpoints of these endpoints, and scaffold thrombosis. Scaffold thrombosis will be defined as acute (< 24 h), subacute (1 to 30 days), late (30 days to 1 year), and very late (beyond 1 year), and the level of evidence (definite or probable) will be based on the ARC definitions [16].

Bleeding events are the secondary endpoint. BARC type 3 or 5 bleeding events at major bleeding events will include fatal bleeding, intracranial hemorrhage, cardiac tamponade, any transfusion with overt bleeding, a reduction in hemoglobin greater than 3 g/dl, and bleeding requiring surgery (excluding dental, nasal, skin, and hemorrhoid surgeries).

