### Plans to promote participant retention and complete follow-up {18b}

Appropriate medical advice can be provided to subjects just in time through message or phone call if they adhere to the protocol and complete follow-up. To those who would be willing to take office visits, proper compensation will be provided. Subjects who suffer from any events or deviate from the protocol will be excluded from the study. However, they will still be monitored and cared for until the end of the study.

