## Statistical analysis

### Statistical analysis of primary and secondary outcomes {20a}

All analyses will be performed on the intention-to-treat (ITT) population. The primary and secondary endpoints that are related to the time to an event will be assessed with Cox survival analysis. The primary analyses will compare the time to event from 12 to 36 months postprocedure between subjects randomized to 36 and 12 months DAPT using the stratified log-rank test. Kaplan‒Meier estimates of MACEs and other endpoints, as well as the 2-sided 95% confidence interval (CI) of the treatment difference in Kaplan‒Meier rates, will be presented for each treatment arm. Other secondary endpoints will be analyzed with the chi-square test or Fisher’s exact test for frequent comparisons. The two-sided significance level will be fixed at 5%. All tests will be performed with SAS version 9.4 (SAS Institute Inc., Cary, North Carolina, US).

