### Analysis methods to handle protocol nonadherence and missing data {20c}

Multiple imputation will be performed to handle missing data. Analysis will be performed based on the ITT population even if there might be crossovers.

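### The retention section excludes subjects who have any event or deviate, with no limit to the time before randomization, against 24-month follow-up of all randomized subjects and ITT analysis

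*Protocol article*

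**What the plan says.** Five parts of the protocol article bear on what happens to a randomized subject after an event or a departure from allocated treatment.

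- Plans to promote participant retention and complete follow-up {18b}: "Subjects who suffer from any events or deviate from the protocol will be excluded from the study". The next sentence adds that these subjects will still be monitored and cared for to the end of the study.
- Follow-up: "All randomized subjects will be followed up for 24 months after randomization".
- Statistical analysis {20a}: "All analyses will be performed on the intention-to-treat (ITT) population". Nonadherence and missing data {20c}: "Analysis will be performed based on the ITT population even if there might be crossovers".
- Criteria for discontinuing or modifying allocated interventions {11b}: "There will be no special criteria for discontinuing or modifying allocated interventions".
- Relevant concomitant care {11d}: "DAPT will be stopped if any BARC type 3 or 5 bleeding events occur and relevant care will be provided".

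**The concern.** The main issue is the exclusion sentence in {18b}. It states a rule about who leaves the study, and that rule is incompatible with the follow-up and analysis rules elsewhere. Its grounds are any event and any deviation, which are outcomes and post-randomization behaviour. Removing randomized subjects on such grounds undoes the comparison that randomization set up. The trial is open label, so sites know the allocation when they decide whether something counts as an event or a deviation. Two conflicting instructions leave room for handling that differs by site or by arm.

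The lesser issue is that the section meant to hold the stopping criteria says there are none, while a mandatory stop for a major bleed stands under concomitant care. DAPT is the allocated treatment of the prolonged arm, so this stop is a discontinuation criterion for that arm.

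**Working it through.** The point rests on text, so the main check is to set the rules side by side.

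**1. Can {18b} and the follow-up and ITT rules all be obeyed?** Take three randomized subjects.

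| Subject | {18b} | Follow-up, {20a}, {20c} |
|---|---|---|
| Has a myocardial infarction at month 20 | Event: excluded | Followed to 24 months after randomization, analysed by ITT |
| Allocated to aspirin, resumes a P2Y12 inhibitor | Deviation: excluded | Crossover: kept in the ITT analysis |
| Allocated to DAPT, BARC 3 bleed, DAPT stopped under {11d} | Event: excluded | Followed and analysed by ITT |

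In each row the two columns conflict on whether the subject stays in the study. The second row is the plainest, because {20c} names crossovers and keeps them.

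**2. Does the promise of continued monitoring resolve it?** Partly. It suggests that information on these subjects would still exist. It does not say that the information enters the endpoint analyses.

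**3. How far does the literal wording reach?** With the planning rates in Sample size {14} (3.5% prolonged, 6.5% standard) and 812 per arm:

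- prolonged: 812 × 0.035 = 28.4 MACE
- standard: 812 × 0.065 = 52.8 MACE
- total: 81.2 with full follow-up

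At 649 per arm, the number needed before the plan allows for 80% follow-up, the total is 649 × 0.035 + 649 × 0.065 = 22.7 + 42.2 = 64.9. All of these subjects have had an event, so the literal sentence covers all of them. If exclusion only means that follow-up ends at the event, first MACE are kept, but MACE after a bleed and later secondary events are lost.

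For major bleeding the document gives no planning rate. If 1% to 5% of the prolonged arm had a BARC 3 or 5 bleed (an assumption), that would be 812 × 0.01 = 8 to 812 × 0.05 = 41 subjects.

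**4. Can the direction of bias be settled?** Suppose only bleeders were dropped. This is narrower than the text and serves only to test the sign. With MACE risk P, bleeding rate p, and share m of bleeders who have a MACE with or after the bleed, the observed risk is (P − p·m)/(1 − p). Assume P = 5% in both arms, and p = 1% on aspirin and 2% on DAPT:

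| m | Aspirin | DAPT | Aspirin minus DAPT |
|---|---|---|---|
| 20% in both | (5 − 0.20)/0.99 = 4.85% | (5 − 0.40)/0.98 = 4.69% | +0.15 points |
| 5% in both | (5 − 0.05)/0.99 = 5.00% | (5 − 0.10)/0.98 = 5.00% | 0 |
| 2% in both | (5 − 0.02)/0.99 = 5.03% | (5 − 0.04)/0.98 = 5.06% | −0.03 points |
| 50% aspirin, 20% DAPT | (5 − 0.50)/0.99 = 4.55% | (5 − 0.40)/0.98 = 4.69% | −0.15 points |

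The sign changes with m, and the document gives neither p nor m.

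**5. {11b} against {11d}.** The stop in {11d} is unconditional for a named event. {11b} does not order DAPT to continue, so treatment of the subject is not in doubt. The rule is simply denied in the section where a site would look for it.

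**The case against.** The strongest reply is that the exclusion sentence was meant for the observational year before randomization. Sample size {14} allows for 12% who cannot be randomized because of an event or withdrawal, in wording close to that of {18b}, and Intervention description {11a} requires subjects to be event-free at 12 months. The literal alternative is also absurd: it would remove every primary event from a time-to-event trial, and a subject with a fatal bleed cannot go on being monitored and cared for. On this view the ITT statements, made twice, plainly govern the analysis.

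This reading is plausible and may well be the intent. But {18b} does not say so. It stands under a heading on retention and complete follow-up, and {11a} already sets the pre-randomization rule. Sites would act on the sentence as written.

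On {11b} and {11d} the reply largely succeeds. The stop itself is unambiguous, and the mismatch is mainly one of filing.

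A reader might also infer that the exclusion would favour prolonged DAPT, since the Background says of metallic drug-eluting stents that "extending therapy beyond 1 year conferred an increased risk of bleeding", and the Outcomes section says "BARC type 3 or 5 bleeding events at major bleeding events will include fatal bleeding", so that a fatal bleed is also a MACE through all-cause death. The documents do not support a firm direction. The Background warns that experience with those stents may not carry over to scaffolds. The Discussion cites a trial with low and similar major bleeding in both groups, and says that earlier scaffold trials collected no bleeding data. Crossovers are foreseen, and the deviation ground could remove subjects from either arm.

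**Conclusion.** The exclusion sentence in {18b} is a wrongly stated rule. It contradicts follow-up of all randomized subjects and ITT analysis despite crossovers, and it should be corrected. This rests on the wording alone and needs no assumption about rates.

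The size and direction of any resulting bias cannot be determined from the document. What can be said is that exclusions tied to bleeding or deviation could be unequal between arms in an open-label trial. The loss of all 81 planned MACE is the extreme of the literal wording and should not be read as what the plan intends or as a forecast. Nor does the document show that the analysis would in fact drop these subjects; it shows that the instructions conflict.

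The mismatch between {11b} and {11d} is secondary: a misplaced rule to be stated in the right section, with no effect on how a bleeding subject is treated.

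**What to change.** 1. In {18b}, replace the exclusion sentence, covering both its event and its deviation grounds, with: *All randomized subjects remain in follow-up to 24 months after randomization and in the ITT analysis, whatever event, treatment change or deviation occurs.* If the sentence was meant only for the period before randomization, limit it to that period explicitly.
2. In {11b}, replace the statement that no criteria exist with one naming the stop of DAPT after a BARC type 3 or 5 bleed as a protocol-specified discontinuation, with a reference to {11d}. This also makes clear that such a stop is not a deviation.

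The cost is two wording changes. No added visits or data are needed, because the Follow-up section already covers all randomized subjects for 24 months and {18b} already keeps monitoring those it excludes. Trial status says that the study had not begun, so the change can be made before any subject is affected.
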